### Recruitment

2.6

For recruiting the participants, first, informed written consent to participate in the study will be collected from the staff nurses working in the selected hospital’s general wards. Then, to choose a sample of the consented staff nurses from each general ward, the sample will be matched against the inclusion and exclusion criteria. The nurses who do not fulfil the inclusion criteria will be excluded from the study.

Nurse-in-charges from each general ward will be taken conveniently using complete enumeration. The nurse-in-charges who are supervising the participating staff nurses at the time of data collection will only be considered for recruitment. If there is a ward from where no staff nurses are taking part, the researcher will exclude the nurse-in-charge and patients from that ward. A written informed consent for participation will be taken before recruiting.

Patients will also be selected conveniently. Only the patients who are receiving care from the staff nurses participating in the study, during the time of data collection, will be selected from each general ward. One patient (who provides their consent) for each nurse will be selected for the study (1:1). As the study is longitudinal, collecting data from the same patient in the in-patient department is very unlikely. Therefore, data from 80 patients will be collected at each (five) contact point, i.e., at baseline, 3-months pre-intervention, and immediately after the intervention, at 3-month, and 6-month follow-up.

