### Study intervention

2.7

The IESE Program was developed by the investigator with the help and collaboration of experts from the field of EI, Human Resource Development, Nursing, and Psychology. The investigators’ personal experience working as a mental health nurse and a thorough literature search served as the foundation for need analysis and base for intervention development. Also, before developing the training program, the investigator interacted with a group of nurses from the study setting as well as other hospitals to do a need assessment. The investigator asked them about the factors that induces stress, their emotional experiences and emotional requirements at work, and the ways they handle stressful situations. The investigator also interacted with patients and nurse-in-charges and nursing supervisors of two hospitals to understand what their expectations are from nursing services. This allowed the investigator to identify and understand practices and gaps in real world. By combining the findings from the need assessment, and critical observation the framework of the training program was developed. Drafts of the IESE program was shared among the above mentioned experts several times for their suggestions and modifications were made as suggested before finalizing the content of the program. The program was also pilot tested among 12 staff nurses in a different setting to establish its credibility and assess its effectiveness. The investigator has also taken a hands-on certificate training course on Emotional Intelligence to gain an understanding of Emotional Intelligence techniques under the supervision of experts in the field of Emotional Intelligence from EquiPoise, Maharashtra, which is a certified Emotional Intelligence training institute in India.

The IESE program does not instruct the nurses on how to feel; rather, it encourages the nurses to reflect on their mental and emotional health. The investigator will deliver the program through lectures, Power Point presentations, group activities, situation analysis, videos, worksheets, and workbooks. A booklet will be given to the participants for future reference. These materials will be applied for a copyright by the authors. Hence, they have not been uploaded to an approved repository yet.

The IESE program components are divided into four sessions. An outline of the sessions is provided in
Table 2.

**Table 2. T2:** Table showing outline of the IESE Program.

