### Data collection

2.9

Data from the staff nurses, patients, and nurse-in-charges will be collected at baseline and 3-month pre-intervention, and immediately after the intervention, at 3-month, and 6-month follow-up by the investigator. Multiple baselines enable an assessment of whether changes occur after or during an intervention, rather than before or as a result of any extraneous factor (
Dundas, Binder, Hansen, & Stige, 2017). The questionnaires will be completed by the participants on the same day. The investigator will always be present with the participants when they fill in the questionnaire and will provide help to understand the questionnaire’s statements if needed. All the participants will be given a unique code to maintain confidentiality and to make sure that only the participants who have consented to participate complete the questionnaires. The investigator will collect the questionnaires on completion and store them safely in a folder. The investigator has considered an attrition rate of 20% while calculating the sample size, to account for participants who discontinue the intervention or follow-ups. Also, the investigator will maintain an attendance sheet of the participants. Reminders will be sent, and calls will be made to the study participants about upcoming and missed sessions.

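### Patient raters for Secondary 5 are chosen by convenience and differ at every contact point, so a change in who is approached after training cannot be separated from a change in nursing care

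*Protocol article*

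**What the plan says.** The Recruitment section (2.6) gives the rule for choosing patient raters: "Patients will also be selected conveniently". One consenting patient is taken per participating nurse, from those in that nurse's care when data are collected. The section expects new raters each time, since "collecting data from the same patient in the in-patient department is very unlikely", and it plans that "data from 80 patients will be collected at each (five) contact point". Two contact points precede training and three follow it.

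Table 1 (section 2.4) narrows the pool by age, literacy, consciousness, severity of illness, mental illness and length of stay. No section says which patient is taken when a nurse has several who qualify, or how many usually do.

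On roles, section 2.7 states "The investigator will deliver the program through lectures". Section 2.9 has the data on nurses, patients and nurse-in-charges collected before training, directly after it, and "at 3-month, and 6-month follow-up by the investigator". It also places the investigator beside respondents as they fill in the questionnaire. No masked or independent selector is described.

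Table 4 (section 2.8) words Secondary 5 as an examination of change. The Aim (section 1.2) speaks instead of the programme's impact on patients' perception. Section 7 lists the missing control arm and attrition as limitations, but not the choice of patients.

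**The concern.** Eligibility criteria say who may be chosen; a convenience rule leaves open who is chosen. Someone who follows this rule exactly may approach the nearest, most talkative or most content patient, and may do so differently before and after training. No breach and no intent is needed.

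Most designs have some protection against this. A concurrent control arm would share the drift, and repeated ratings by the same patient would cancel stable differences between raters. This design has neither for Secondary 5. A difference between waves is therefore the sum of any change in care and any change in who was asked, and the data cannot split the two. If the difference is then read as the programme's impact on patients, part or all of it could come from the choice of rater.

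**Working it through.** **The plan's own figure.** There is none to reproduce. Section 2.5 says no calculation was made for patients. Its only computed size (50, then 63 after dropout) is for nurses and does not bear on this point.

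**Inputs from the protocol.** 80 patients at each contact point, one per nurse, new patients each time, no control arm.

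**Assumptions, not in the protocol.** No true change in care; independent patients with a common SD; one wave before training compared with one wave after (a simplification of the repeated-measures analysis in section 2.12); *k* eligible patients per nurse; correlation *r* between how favourable a patient looks to the chooser and the rating that patient gives; the most favourable-looking patient taken after training and an arbitrary one before.

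**Step 1, significance threshold.** SE = sqrt(2/80) = 0.158 SD. Threshold = 1.96 × 0.158 = 0.31 SD.

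**Step 2, shift from choice of rater.** Shift = *r* × E[maximum of *k* standard normals]. For *k* = 3 the expected maximum is 0.846.
- *r* = 0.2: 0.2 × 0.846 = 0.17 SD
- *r* = 0.5: 0.5 × 0.846 = 0.42 SD

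**Step 3, break-even correlation.** 0.31 / 0.846 = 0.37. Below this the expected shift stays under the threshold, and that covers more than half of the 0.2 to 0.5 range.

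**Step 4, false-positive rate.** A shift below the threshold still raises the chance of a significant result. By the normal approximation, P = Φ(shift/SE − 1.96) + Φ(−shift/SE − 1.96).
- 0.17 SD: shift/SE = 1.07, P about 19%
- 0.42 SD: shift/SE = 2.68, P about 76%

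**Step 5, selection for only some nurses.** Here the chosen patient truly is the highest rater (*r* = 1), but only for a share *f* of nurses after training. The shift is *f* × E[maximum]. The rates come from a simulation with 4,000 runs per row.

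| *k* | *f* | Shift (SD) | False-positive rate |
|---|---|---|---|
| 2 | 10% | 0.06 | 6% |
| 2 | 25% | 0.14 | 14% |
| 3 | 25% | 0.21 | 27% |
| 3 | 50% | 0.42 | 76% |

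The effect runs from negligible to decisive, depending on quantities the protocol neither reports nor controls.

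**The case against.** Several objections carry weight.

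- **Who picks.** A reader might infer that the investigator personally chooses each rater. Section 2.6 is in the passive and names no one. The inference is reasonable, because no other data collector is named, but it remains an inference. The point survives if ward staff choose, since they too would be likely to know whether training has taken place.
- **How many are eligible.** A reader might infer that several patients per nurse always qualify. The protocol gives no census, and Table 1 together with the requirement of that nurse's care narrows the pool. Where only one patient qualifies, there is nothing to choose.
- **Size.** The illustration is one-sided and extreme: every nurse, after training only. Nothing in the protocol supports that switch or the assumed correlations. It shows what is possible, not what is likely, and not that bias occurred.
- **Two pre-tests.** These are a real strength. They can show drift in the pool of raters before training. They cannot show a shift that begins with training.
- **Already disclosed.** Convenience selection is stated openly, and the missing control arm is called a major limitation, which already weakens attribution. But that limitation does not tell the reader that the raters themselves may differ between waves.
- **Condensed article.** Bedside detail may be left to a full protocol. The selection rule, however, is stated here, so the point concerns a declared choice and not an omission.

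**Conclusion.** The concern holds in a limited form. For Secondary 5, convenience choice of a new patient per nurse at each contact point, with data collected by someone who delivers the programme and knows the timing, leaves rater selection mixed with any change in care. No feature of the design separates the two after training.

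The worst-case shift is 0.17 to 0.42 SD against a threshold of about 0.31 SD, crossed in expectation only if the correlation exceeds about 0.37. This rests on three eligible patients per nurse and a switch confined to the visits after training, both assumed. With weaker selection the effect can be trivial.

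The documents do not support the stronger readings that the investigator is known to pick the raters, that bias took place, or that its direction is settled. The nurse-reported outcomes, Secondary 1 to 4, are not touched by this point.

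**What to change.** **As a design rule:** at each of the five contact points, list the paired nurse's patients who meet Table 1, approach them in a pre-generated random order, take the first who consents, and log everyone approached and everyone who refuses. The cost is a list and a short log per visit, plus a little ward time when a patient declines; no extra patients or staff are needed. This reduces selection bias but does not fully remove it. Refusal may still differ before and after training, though the log would make that visible.

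**For this cohort:** section 9 reports that follow-up data collection was completed in May 2022, so the rule can no longer be applied. If patients were in fact chosen by convenience, add rater selection to the limitations in section 7 and report Secondary 5 as a descriptive change between different groups of patients, not attributable to the programme. The statement in section 1.2 about impact on patients' perception should be reworded to match. This costs a few sentences.

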### Sample size and selection

2.5

For the current study, all staff nurses working in the general wards will have the probability of being selected. At a 20% dropout rate, 80% power, SD of 12.3 (taken after feasibility study), and clinically significant difference of 5, it was calculated that approximately 63 staff nurses should be recruited for the current study. However, to reduce the chances of higher attrition due to the unpredictable nature of the hospital environment, the researchers decided to recruite 80 staff nurses.

$$n=\frac{{\left[Z_{1-\frac{\alpha }{2}}+Z_{1-\beta }\;\right]}^{2}\sigma^{2}}{d^{2}}$$

*n* = minimum sample size required

$Z_{1-\frac{\alpha }{2}}$
 = 1.96 at
*α* = 0.05

$Z_{1-\beta }$
 = 0.84 at 80% power

*σ* = population SD of the outcome variable = 12.3

*d* = clinically significant difference = 5

$$∴n=\frac{{\left(1.96+0.84\right)}^{2}{\left(12.3\right)}^{2}}{5^{2}}=50$$

With 20% drop out rate

$$n*=\frac{n}{1-0.3}\;=\frac{50}{0.2}=63\;\left(\text{approx}.\right)$$

As nurse-in-charges of all the general wards of the selected hospital will be approached for their consent to participate using complete enumeration, a sample size calculation was not performed. Similarly, a sample calculation was not performed for patients, because only those in-patients who will be receiving care from the recruited staff nurses will be approached for their consent to participate in the study.

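### The 80 patients stated for each of five waves is a ceiling that holds only if no nurse is lost; at the plan's own 20% attrition about 64 are available at the last wave

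*Protocol article*

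**What the plan says.** Section 2.5 (Sample size and selection) derives a requirement of 63 nurses, which includes a 20% dropout allowance. It then says that "the researchers decided to recruite 80 staff nurses", and gives the reason: "to reduce the chances of higher attrition due to the unpredictable nature of the hospital environment". It adds that no sample size was calculated for patients.

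Section 2.6 (Recruitment) sets the rules for patients. On eligibility: "Only the patients who are receiving care from the staff nurses participating in the study, during the time of data collection, will be selected". The ratio is one consenting patient to one nurse. Because the same in-patient is unlikely to be found again at a later wave, the section concludes that "data from 80 patients will be collected at each (five) contact point".

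Section 2.9 (Data collection) returns to attrition: "The investigator has considered an attrition rate of 20% while calculating the sample size", with the purpose "to account for participants who discontinue the intervention or follow-ups". Section 7 (Strengths and Limitations) names higher attrition as a possible limitation. No section describes replacing lost nurses, relaxing the 1:1 ratio, or a lower patient count at later waves.

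**The concern.** Section 2.6 argues from patient turnover to a fresh set of 80 patients at every wave. It does not consider nurse turnover, although patients are reached only through nurses. Four statements are in play: 80 nurses, one patient each, patients only of participating nurses, and 80 patients at all five waves. Once any nurse stops participating, they cannot all hold.

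Two things follow. First, the patient number stated for Secondary 5 (change in patients' perception of nursing care) is a maximum presented as a plan. A team trying to meet it after losses would have to take second patients from some nurses or use patients of nurses who had left, and either departs from section 2.6.

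Second, patients differ at each wave and there is no control arm, so the nurse is the only unit that links patient scores before and after training. If 1:1 is kept, the earlier waves include patients of nurses who later leave and the later waves do not. The wave means could then move for a reason unrelated to the programme.

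**Working it through.** **Inputs.** 80 nurses recruited (2.5); one patient per nurse (2.6); five contact points (2.6); 20% attrition (2.5 and 2.9). The timing of attrition is not given, so the per-wave counts after baseline are scenarios.

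**The plan's own figure.** 80 nurses x 1 patient = 80 per wave, and 80 x 5 = 400 in total. This reproduces exactly, with zero nurse loss.

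**Where the 20% enters.** 50 / (1 - 0.20) = 62.5, which gives the stated 63. (The denominators printed in that line of 2.5 do not give 63; only 0.8 does. That is a separate matter and does not affect this point.) The allowance was used to go from 50 to 63. It was not applied to 80.

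**Patients at the last wave, 80 x (1 - loss) x 1:**

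| Nurse loss by 6 months | Patients at 6 months |
|---|---|
| 0% | 80 |
| 5% | 76 |
| 10% | 72 |
| 20% | 64 |
| 30% | 56 |

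At 20% the last wave is 80 - 64 = 16 short. To reach 80 from 64 nurses takes 80 / 64 = 1.25 patients per nurse. To keep 1:1 and still have 80 takes 80 / 0.80 = 100 nurses recruited.

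**Five-wave total at 20% loss, by assumed timing:**

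| Timing | Counts | Total |
|---|---|---|
| All just before the last wave | 4 x 80 + 64 | 384 |
| Evenly across waves | 80 + 76 + 72 + 68 + 64 | 360 |
| All around the training | 80 + 80 + 3 x 64 | 352 |
| All just after baseline | 80 + 4 x 64 | 336 |

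Against 400 this is 4% to 16% fewer (16/400 to 64/400).

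**Precision.** This is the 95% half-width, in SD units, for the difference between two wave means, with patients treated as independent:
- 80 against 80: 1.96 x sqrt(1/80 + 1/80) = 0.310
- 80 against 64: 1.96 x sqrt(1/80 + 1/64) = 0.329

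**Change in nurse mix.** Suppose 20% of nurses leave and their patients score lower by an amount D than patients of nurses who stay. D is an assumption; the article gives no figure. The full-roster mean is then 0.20 x D below the mean for stayers, so losing the leavers raises the later mean by 0.20 x D with no programme effect:
- D = 0: no shift
- D = 0.2 SD: 0.04 SD
- D = 0.5 SD: 0.10 SD
- D = 0.8 SD: 0.16 SD

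If patients of leavers scored higher, the shift would run the other way.

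**The case against.** The strongest reply is that 80 is the ordinary nominal count, one patient per recruited nurse before attrition. It is correct at baseline and the arithmetic is sound. That stands, and the fault is in stating the same 80 without qualification for every wave.

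The 20% is also a planning allowance and not a forecast. A reader might infer that 80 cannot be reached at all. The documents do not support that: nothing predicts 64 nurses at any wave, and with full retention 80 is attainable. The shortfall is conditional on loss.

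Nor does losing 16 nurses strictly mean losing 16 patients. Sections 2.4 and 2.5 refer to patients of the recruited nurses, and the attrition in 2.9 covers leaving the intervention or the follow-ups. A nurse who skips a questionnaire but still works on the ward might still have a patient surveyed. Section 2.6 is narrower, since it speaks of nurses participating in the study, but the article does not settle the case. A nurse who withdraws is lost under 2.6.

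A reader might also infer that Secondary 5 is now too small. No patient sample size was calculated, so no stated power is invalidated, and the loss of precision is minor.

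Finally, analysis detail is commonly left to a fuller document that is not shown. The absence of that detail is therefore not the finding; the finding is a printed number that conflicts with the article's own sampling rule once the attrition it allows for occurs.

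**Conclusion.** The point holds in a limited form. Under sections 2.5 and 2.6 as written, 80 patients per wave is an upper bound, met only with no nurse loss. If the plan's own 20% occurs, about 64 patients are available at 6 months and about 336 to 384 in total, against an implied 400. These figures assume that a nurse who is lost contributes no further patient, and the range reflects the unstated timing.

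The statistical consequence for size is small. The nurse sample is not threatened either: 64 nurses still exceed the 50 required, and the margin lasts until 37.5% loss (1 - 50/80).

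The consequence for comparability is possible but unquantified. A reader might infer that the patient results are biased by a definite amount. The documents give no difference between patients of leavers and stayers, so 0.04 to 0.16 SD is illustration under an assumed 0.2 to 0.8 SD difference, and the shift is nil if there is none. This is a correction worth making, and it does not undermine the study.

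**What to change.** **Section 2.6.** Restate the patient sample as one patient per nurse still participating at each wave, up to 80, with about 64 expected at 6 months under 20% attrition. Say that numbers will not be made up outside the 1:1 rule. Section 9 says follow-up data collection was completed in May 2022, so the actual count per wave can be reported, together with whether 1:1 was kept.

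**Section 2.12.** For patient scores, name a mixed model with wave as a fixed effect and nurse as a random effect, using all patients. The stated repeated measures ANOVA does not suit this outcome with the patient as the repeated unit, because different patients are measured at each wave; the nurse is what repeats. Add a sensitivity analysis limited to nurses who contribute patients both before and after training. It should not be the main analysis, because it discards data and keeps only nurses who stayed.

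**Cost.** A less favourable stated number and a sentence or two on analysis. The model needs each patient form to be linked to its nurse. Section 2.9 gives participants unique codes but does not say that patient forms carry the nurse's code, so this must be confirmed. If they do, no new data are needed.

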### Study intervention

2.7

The IESE Program was developed by the investigator with the help and collaboration of experts from the field of EI, Human Resource Development, Nursing, and Psychology. The investigators’ personal experience working as a mental health nurse and a thorough literature search served as the foundation for need analysis and base for intervention development. Also, before developing the training program, the investigator interacted with a group of nurses from the study setting as well as other hospitals to do a need assessment. The investigator asked them about the factors that induces stress, their emotional experiences and emotional requirements at work, and the ways they handle stressful situations. The investigator also interacted with patients and nurse-in-charges and nursing supervisors of two hospitals to understand what their expectations are from nursing services. This allowed the investigator to identify and understand practices and gaps in real world. By combining the findings from the need assessment, and critical observation the framework of the training program was developed. Drafts of the IESE program was shared among the above mentioned experts several times for their suggestions and modifications were made as suggested before finalizing the content of the program. The program was also pilot tested among 12 staff nurses in a different setting to establish its credibility and assess its effectiveness. The investigator has also taken a hands-on certificate training course on Emotional Intelligence to gain an understanding of Emotional Intelligence techniques under the supervision of experts in the field of Emotional Intelligence from EquiPoise, Maharashtra, which is a certified Emotional Intelligence training institute in India.

The IESE program does not instruct the nurses on how to feel; rather, it encourages the nurses to reflect on their mental and emotional health. The investigator will deliver the program through lectures, Power Point presentations, group activities, situation analysis, videos, worksheets, and workbooks. A booklet will be given to the participants for future reference. These materials will be applied for a copyright by the authors. Hence, they have not been uploaded to an approved repository yet.

The IESE program components are divided into four sessions. An outline of the sessions is provided in
Table 2.

**Table 2. T2:** Table showing outline of the IESE Program.

Session	Outline of the content	Duration
I	1. Understanding emotions, intelligence and emotional intelligence a. What is emotion? b. Views on emotion: the old and new paradigms c. How are emotions formed? d. The Plutchik model of emotion e. What is intelligence? f. The types of intelligence 2. The concept of Emotional Intelligence a. The importance of emotional intelligence	2 hour
II	1. The neuroscience behind emotional intelligence a. Basic brain structure and their function b. Parts of the brain that are associated with emotions c. Emotional/amygdala hijack 2. GENOS Model of Emotional Intelligence 3. Core components of emotional intelligence skills	2 hours
III	1. Emotional literacy 2. Interpersonal relationship, sympathy and empathy a. Importance of empathy in healthcare b. Effective interpersonal communication techniques 3. Concept of Emotional Labour and Self-Compassion	2 hours
IV	1. Concept of motivation and developing gratitude 2. Management of difficult emotions: anger and stress 3. Management of difficult emotions: anxiety and sadness	2 hours

To provide the IESE program without disrupting the work environment of the hospital, the consented nurses will be divided into smaller groups of 5-10, so that the participants engage in the activities of the training program with more efficiency. Each group will be given the same IESE program in similar setting and using similar techniques. Nurses in each group will complete a total of eight hours of training (two hours each day for four days) at the end of the intervention program. If a participant misses any session, he/she will be accommodated in another group to complete the missed session. The sessions will be made flexible and accommodating. The investigator will make sure that the IESE program does not overlap with the staff nurses’ daily work schedule and hamper the hospital activities or disturb the patients. The nurse-in-charges, staff nurses, and the nurse-supervisors will be informed many weeks prior to starting the program to effectively make the duty roster. The investigator will collect the e-mail address and phone numbers of the participants, for sending reminders about the sessions, and follow-up.
Table 3 shows an overview of the time plan. The project will be implemented from approximately January 2021 to May 2022, with a total duration of 17 months (which includes data collection and intervention implementation).

**Table 3. T3:** Table showing the timeline of the current study.

	Study period							
	Enrolment	Pre-test		Intervention	Post-test			Analysis
Time point		T _0_ (Baseline)	T _-1_ (3-month)		T _1_ (Immediately after the intervention)	T _2_ (3-month)	T _3_ (6-month)	
Enrolment	✓							
Eligibility screen	✓							
Informed consent	✓							
Intervention				4 sessions of 2 hours each.				
Assessments of study variables		✓	✓		✓	✓	✓	
Final data analysis and dissemination								

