### Design

2.2

The current study has a quasi-experimental (one-group) design, which involves staff nurses working in the general wards of a selected hospital. The present study’s design is well suited, keeping in mind the work shifts of staff nurses and the number of staff nurses in the selected hospital. To derive a better understanding of whether intervention on emotional well-being components would affect staff nurses and the perception of patients and nurse-in-charges, the current study has based its concept on Neuman’s System Model and King’s Interacting Systems Theory to design the conceptual framework. Both of these theories have been proven effective in providing guidance for applying the theoretical understanding to practical clinical nursing situations to improve practice (
Montano, 2021;
Shanta & Connoly, 2013).

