### Statistical analysis

2.12

Mean and standard deviation will be used to describe measurement data. Frequencies and percentages will be used to represent count data. Repeated measures ANOVA will be used to analyze the effect of the training program. Chi-square will be used to see if an association between the variables before is after the training program.

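### The stated repeated measures ANOVA and the sample size make no allowance for nurses in the same training group or ward changing together; if they do, standard errors are too small

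*Protocol article*

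**What the plan says.** All references are to the protocol article.

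- **Design:** "The current study has a quasi-experimental (one-group) design". The effect therefore rests wholly on change over time in the trained nurses.
- **Study intervention:** "the consented nurses will be divided into smaller groups of 5-10". A group completes four two-hour sessions, partly through group activities. All groups are to get the same programme in similar settings, delivered by the investigator. For absences: "If a participant misses any session, he/she will be accommodated in another group to complete the missed session".
- **Study participants** and **Recruitment:** nurses come from the hospital's general wards, so several can share a ward. For supervisors: "Nurse-in-charges from each general ward will be taken conveniently using complete enumeration".
- **Sample size and selection:** "At a 20% dropout rate, 80% power, SD of 12.3 (taken after feasibility study), and clinically significant difference of 5" are the inputs, from which "it was calculated that approximately 63 staff nurses should be recruited for the current study"; then "the researchers decided to recruite 80 staff nurses". The formula has no design effect.
- **Statistical analysis:** "Repeated measures ANOVA will be used to analyze the effect of the training program". No term for training group or ward is named.
- **Data collection measures/instruments:** ward or unit is recorded as a demographic variable, but no use of it in the effect analysis is stated.

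**The concern.** A repeated measures ANOVA with the nurse as subject removes each nurse's own level and models the correlation among that nurse's scores. It still assumes that one nurse's change tells us nothing about another's. Two features of the design put that in doubt. Members of a training group go through the same interactive sessions together. Ward colleagues share workload and roster, in a period that the article itself describes as one of pandemic and scarce staff. Either can move the scores of several nurses together between the pre-test and post-test periods.

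With no control arm, stable differences between wards or groups cancel out of each nurse's change, so only shared *change* matters. Where it exists, the mean change is less precise than the ANOVA reports: confidence intervals are too narrow and a nominal 5% test rejects too often.

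**Working it through.** **1. The plan's own sample size.** Inputs from Sample size and selection: z-values 1.96 and 0.84, SD 12.3, difference 5.

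n = (1.96 + 0.84)² × 12.3² / 5² = 7.84 × 151.29 / 25 = 47.4, so 48. The article prints 50, which is what a t-based version of the same calculation gives (power 0.796 at 49, 0.8045 at 50). Then 50 / (1 − 0.2) = 62.5, so 63 as stated. (The printed dropout line shows other divisors, 1 − 0.3 and 0.2; these give 71 and 250 and are misprints.) The calculation reproduces as one for independent nurses, with a design effect of 1.

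**2. Number and size of clusters.** 80 nurses in groups of 5 to 10 make 80/10 = 8 to 80/5 = 16 groups. With the planned 20% attrition, 80 × 0.8 = 64 complete, which is 64/16 = 4 to 64/8 = 8 per group.

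**3. Effect of shared change.** With m completers per group and ICC ρ of the change score:

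- design effect DE = 1 + (m − 1)ρ
- true SE = unadjusted SE × √DE
- true two-sided type I error = 2 × [1 − Φ(1.96/√DE)]
- power at 64 completers = Φ(5 / (12.3 × √(DE/64)) − 1.96), taking 12.3 as the SD of change, as the plan's formula does

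The article gives no ICC; 0 to 0.10 is an assumption.

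| m | ρ | DE | True SE / unadjusted SE | Type I error | Power at n = 64 |
|---|---|---|---|---|---|
| any | 0 | 1.00 | 1.00 | 5.0% | 0.90 |
| 4 | 0.05 | 1.15 | 1.07 | 6.8% | 0.86 |
| 4 | 0.10 | 1.30 | 1.14 | 8.6% | 0.81 |
| 8 | 0.05 | 1.35 | 1.16 | 9.2% | 0.80 |
| 8 | 0.10 | 1.70 | 1.30 | 13.3% | 0.70 |
| 10 (full group, no loss within it) | 0.05 | 1.45 | 1.20 | 10.4% | 0.77 |
| 10 (full group, no loss within it) | 0.10 | 1.90 | 1.38 | 15.5% | 0.66 |

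The last two rows use the largest group size with the same 64 nurses, as an outer bound.

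**4. Limits of the table.** It covers training groups only; the number of nurses per ward is not given, so ward clustering cannot be sized in the same way. It uses a normal reference; with 8 to 16 groups a correct test would also have far fewer degrees of freedom than one counting nurses.

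**The case against.** *The ANOVA already deals with correlation.* In part. It deals with correlation within a nurse, so a reader who infers that every rating is treated as independent goes too far. The gap is correlation of change between nurses.

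*The understatement is not shown.* This stands as a limit on size. At ICC 0 nothing changes, and the article offers no ICC of change. One investigator delivering the same programme to every group, with missed sessions made up elsewhere, may keep training-group clustering small. If the training affected nobody, group dynamics would add no shared change; inflated type I error then needs ward or calendar effects, or group effects that average out to zero. A reader might infer that standard errors are certainly too small; the document supports only that they will be if changes are positively correlated.

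*Supervisors rating several nurses each adds a further layer.* A reader might infer this, but the article does not say it. Nurse-in-charges are enrolled as respondents in their own right, and the outcome is their perception of nursing care. If each gives one rating per time point, the rater is already the unit and there is no problem.

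*Recruiting 80 rather than 63 gives headroom.* For power, partly: at 64 completers power stays at 0.80 or above up to ICC 0.05 with 8 per group, and falls to 0.70 at ICC 0.10. Extra nurses do not correct a standard error computed under the wrong assumption.

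*Cluster terms belong in an analysis plan, which is not shown.* A fuller plan could add them. But the article names the method and prints the formula, and both as written assume independent nurses.

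*The missing control arm matters more.* True for attributing change to the programme, and the article acknowledges it. It is a separate matter from whether the intervals are right.

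**Conclusion.** The point holds as a conditional one. Nurses are trained in groups and share wards, and neither the named analysis nor the sample size allows for correlation of change within either. With about 64 completers, 4 to 8 per group, and an assumed ICC of change of 0 to 0.10, the design effect is 1.0 to 1.7 and the true type I error 5% to about 13%, with 15.5% as an outer bound for full groups of 10. The figures rest on the assumed ICC, equal group sizes and a normal reference. They do not show that the error is inflated in this trial, only that the stated analysis has no protection if changes are clustered. Study status reports that follow-up is complete, so the sample size cannot be changed; the analysis can.

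**What to change.** In Statistical analysis (2.12):

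1. For the nurse outcomes, replace the repeated measures ANOVA with a linear mixed model with a random nurse effect and a random training-group-by-period effect. A group intercept alone would adjust level, not change.
2. For ward, add a random ward-by-period effect, or give a sensitivity analysis clustered by ward. Ward as a plain main effect would not address shared change.
3. Use Satterthwaite or Kenward-Roger degrees of freedom, given only 8 to 16 groups.
4. Record each nurse's original training group and analyse the nurse in it, even if a session was made up elsewhere. Ward is already collected. The article mentions an attendance sheet but does not say that it records group, so this must be confirmed.
5. State how nurse-in-charges rate. If one rates more than one nurse, account for clustering by rater; if each gives one rating per time point, no change is needed there.

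**Cost:** a few sentences and one extra variable. Intervals would widen, with a standard error up to about 30% larger at ICC 0.10 and 8 completers per group (√1.7 = 1.30), and degrees of freedom would fall. If clustering is negligible, the results would change little.
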